# Efficacy of personalized repetitive transcranial magnetic stimulation based on functional reserve to enhance ambulatory function in patients with Parkinson’s disease: study protocol for a randomized controlled trial

**DOI:** 10.1186/s13063-024-08385-2

**Published:** 2024-08-16

**Keywords:** Functional reserve, Gait, Repetitive transcranial magnetic stimulation, Parkinson’s disease

## Abstract

**Background:**

Repetitive transcranial magnetic stimulation (rTMS) is one of the non-invasive brain stimulations that modulate cortical excitability through magnetic pulses. However, the effects of rTMS on Parkinson’s disease (PD) have yielded mixed results, influenced by factors including various rTMS stimulation parameters as well as the clinical characteristics of patients with PD. There is no clear evidence regarding which patients should be applied with which parameters of rTMS. The study aims to investigate the efficacy and safety of personalized rTMS in patients with PD, focusing on individual functional reserves to improve ambulatory function.

**Methods:**

This is a prospective, exploratory, multi-center, single-blind, parallel-group, randomized controlled trial. Sixty patients with PD will be recruited for this study. This study comprises two sub-studies, each structured as a two-arm trial. Participants are classified into sub-studies based on their functional reserves for ambulatory function, into either the motor or cognitive priority group. The Timed-Up and Go (TUG) test is employed under both single and cognitive dual-task conditions (serial 3 subtraction). The motor dual-task effect, using stride length, and the cognitive dual-task effect, using the correct response rate of subtraction, are calculated. In the motor priority group, high-frequency rTMS targets the primary motor cortex of the lower limb, whereas the cognitive priority group receives rTMS over the left dorsolateral prefrontal cortex. The active comparator for each sub-study is bilateral rTMS of the primary motor cortex of the upper limb. Over 4 weeks, the participants will undergo 10 rTMS sessions, with evaluations conducted pre-intervention, mid-intervention, immediately post-intervention, and at 2-month follow-up. The primary outcome is a change in TUG time between the pre- and immediate post-intervention evaluations. The secondary outcome variables are the TUG under cognitive dual-task conditions, Movement Disorder Society-Unified Parkinson’s Disease Rating Scale Part III, New Freezing of Gait Questionnaire, Digit Span, trail-making test, transcranial magnetic stimulation-induced motor-evoked potentials, diffusion tensor imaging, and resting state functional magnetic resonance imaging.

**Discussion:**

The study will reveal the effect of personalized rTMS based on functional reserve compared to the conventional rTMS approach in PD. Furthermore, the findings of this study may provide empirical evidence for an rTMS protocol tailored to individual functional reserves to enhance ambulatory function in patients with PD.

**Trial registration:**

ClinicalTrials.gov NCT06350617. Registered on 5 April 2024.

**Supplementary Information:**

The online version contains supplementary material available at 10.1186/s13063-024-08385-2.

## Introduction

### Background and rationale {6a}

Parkinson’s disease (PD) is the second most common neurodegenerative disorder, characterized by cardinal symptoms including resting tremor, bradykinesia, and rigidity, alongside non-motor symptoms such as cognitive impairment, depression, and autonomic dysfunction [1]. The current gold standard treatment for PD involves dopaminergic medications, which alleviate symptoms without impeding disease progression [2]. However, prolonged use of these medications may lead to complications such as levodopa-induced dyskinesia [3]. Surgical interventions, such as deep brain stimulation of the subthalamic nucleus or globus pallidus interna, are available for some patients, although eligibility is limited [4]. The global prevalence of PD is increasing, which is attributable to the rapid expansion of the aging population [5]. Therefore, ongoing research into disease-modifying therapies is necessary to manage symptoms and slow disease progression.

Repetitive transcranial magnetic stimulation (rTMS) is a non-invasive brain stimulation that modulates cortical excitability through magnetic pulses [6]. In PD, rTMS has been employed to enhance motor and gait function by targeting areas such as the primary motor cortex (M1), dorsolateral prefrontal cortex (DLPFC), supplementary motor area (SMA), and cerebellum using various stimulation parameters [7–9]. High-frequency rTMS over the M1, DLPFC, and SMA has demonstrated positive effects on overall motor symptoms in PD [9]. While an increase in dopamine secretion in the basal ganglia via the cortico-striatal pathways may contribute to improvements in motor function, the precise underlying mechanism of rTMS in PD remains to be elucidated [10, 11]. Conversely, intermittent theta burst stimulation of the M1 and DLPFC, or high-frequency rTMS of the bilateral motor cortex, does not significantly benefit motor function in PD [12, 13]. Likewise, research on the application of varied rTMS methodologies to enhance motor function in PD has been conducted, yielding diverse outcomes based on these rTMS approaches (Table 1).

**Table 1 Tab1:** Characteristics of randomized controlled trials applying high-frequency repetitive transcranial magnetic stimulation to improve motor function in Parkinson’s disease

Study	Site	Stimulation order	Frequency	Intensity	Session	Sample size	Control	Motor outcome
Benninger, 2012 [12]	Bilateral M1-UL	Alternating	50	AMT 80%	8	26	Sham (13 vs 13)	10MWT ( −) UPDRS III ( −)
Brys, 2016 [14]	Bilateral M1-UL	Sequential (L → R)	10	RMT	10	29	Sham on DLPFC (14 vs 15)	UPDRS III ( +)
Khedr, 2019 [15]	Bilateral M1-UL	Sequential (R → L)	20	RMT 90%	10	30	Sham (19 vs 11)	UPDRS III ( +)
Spagnolo, 2021 [16]	Bilateral M1-UL	More affected, but bilaterally	10	RMT 90%	12	20	Sham on PFC (20 vs 20)	UPDRS III ( +)
Makkos, 2016 [17]	Bilateral M1-UL	Sequential (R → L)	5	RMT 90%	10	23	Sham on PFC (21 vs 20)	TUG ( −) UPDRS III ( +) HY ( −)
Yokoe, 2018 [18]	Bilateral M1-UL	Sequential (less affected → more affected)	10	RMT 100%	1	19	Crossover	UPDRS III ( +)
Li, 2020 [19]	M1-UL	Contralateral where feeling pain bilateral pain → left M1	20	RMT 80%	5	48	Sham (24 vs 24)	UPDRS III ( +)
Chang, 2016 [20]	M1-LL	Dominant hemisphere	10	RMT 90%	5	8	Crossover (2 weeks wash-out)	TUG ( +) UPDRS III ( +)
Kim, 2015 [21]	M1-LL	Dominant hemisphere	10	RMT 90%	5	17	Crossover (2 weeks wash-out)	TUG ( +) UPDRS III ( +)
Maruo, 2013 [22]	Bilateral M1-LL	Sequential (more affected → less affected)	10	RMT 100%	3	21	Crossover	10MWT ( +) UPDRS III ( +) Finger tapping ( +)
Chung, 2020 [23]	Bilateral M1-LL	Sequential (more affected → less affected)	25	RMT 80%	12	33	Sham (17 vs 16)	10MWT ( +) 7 m TUG ( +) 7 m TUG-Cog ( +) UPDRS III ( +)
Yang, 2013 [24]	M1-LL	Contralaterally to the more affected side	5	RMT 100%	12	20	Sham (10 vs 10)	10MWT-comfortable speed ( −) 10MWT-fast speed ( +) TUG ( +)
Khedr, 2003 [25]	M1-LL, bilateral M1-UL	Sequential (R → L)	5	MT 120% for hand	10	36	Sham (19 vs 17)	Gait speed ( +) UPDRS III ( +)
Brys, 2016 [14]	Left DLPFC	-	10	RMT	10	27	Sham on DLPFC (12 vs 15)	UPDRS III ( −)
Pal, 2010 [26]	Left DLPFC	-	5	RMT 90%	10	22	Sham (12 vs 10)	UPDRS III ( −)
del Olmo, 2007 [27]	DLPFC	Contralaterally to the more affected side	10	RMT 90%	10	13	Sham (8 vs 5)	Gait ( −) Finger tapping ( +)
Yokoe, 2018 [18]	DLPFC	Sequential (less affected → more affected)	10	RMT 100%	1	19	Crossover	UPDRS III ( −)
Brys, 2016 [14]	M1-UL and left DLPFC	Left DLFPC → bilateral M1 (L → R)	10	RMT	10	35	Sham on DLPFC (20 vs 15)	UPDRS III ( −)
Lomarev, 2006 [28]	Bilateral M1-UL and bilateral DLPFC	L → R	25	RMT 100%	8	16	Sham (7 vs 9)	10MWT ( +)
Spagnolo, 2021 [16]	M1-UL and PFC	M1-UL → PFC more affected, but bilaterally	10	(M1) RMT 90% (PFC) RMT 100%	12	19	Sham on PFC (20 vs 20)	UPDRS III ( +)

*M1-UL* Primary motor cortex in the upper limb, *AMT* Active motor threshold, *10MWT* 10-m walk test, *UPDRS* Unified Parkinson’s Disease Rating Scale, *L* Left, *R* Right, *RMT* Resting motor threshold, *DLPFC* Dorsolateral prefrontal cortex, *PFC* Prefrontal cortex, *TUG* Timed-Up and Go, *HY* Hoehn and Yahr scale, *M1-LL* Primary motor cortex in the lower limb, *TUG-Cog* Timed-Up and Go under cognitive dual-task condition, *MT* Motor threshold, *M1* Primary motor cortex

rTMS applied to the DLPFC also alleviates the non-motor symptoms of PD, such as depression and cognitive impairment [29]. Multiple sessions of high-frequency rTMS targeted at the DLPFC could enhance executive function in PD [26, 30]. In contrast, high-frequency rTMS of the left DLPFC leads to a non-significant reduction in depressive mood among patients with PD [14]. The exact rationale behind these varied responses in PD to rTMS treatment remains speculative, highlighting the need for further research to uncover the underlying mechanisms thereof. The effects of rTMS in PD have yielded mixed results, influenced by factors including the rTMS stimulation site, frequency, intensity, total number of pulses, and the number of sessions, as well as clinical subtypes of patients with PD [15, 31]. Furthermore, variability in the extent of basal ganglia damage among patients presents challenges in achieving consistent outcomes with standardized rTMS treatment protocols. A personalized rTMS approach targeting heterogeneous patient’ characteristics, including the presence of tremors, freezing, motor fluctuation, and dyskinesia may be necessary to maximize the effect of rTMS [7].

Recently, the concept of functional reserve has been proposed for patients with PD [32]. This concept emerged from the manifestation of inconsistent symptoms in patients with similar degrees of nigrostriatal dopaminergic deficits from dopamine transporter (DAT) imaging [23]. In a study assessing motor functional reserve using the Movement Disorder Society-Unified Parkinson’s Disease Rating Scale (MDS-UPDRS) Part III and DAT, functional connectivity analysis using resting-state functional magnetic resonance imaging (rsfMRI) confirmed that motor functional reserve was associated with the functional connectivity of brain networks in PD, involving structures such as the basal ganglia and inferior frontal lobe. Another study found an association between motor functional reserve in PD and striatal volume [33]. Hence, it is conceivable that the motor function reserve in PD is related to the neural network connectivity in the basal ganglia and frontal lobe. Additionally, the concept of resilience in patients with PD includes the cognitive functional reserve. Therefore, targeting functional improvement based on individual functional reserve, which encompasses motor and cognitive functions, as well as the degree of structural damage to the brain, is necessary for the management of PD [32].

Single-and dual-task assessments are primarily utilized to discern functional reserves in patients with PD [34]. In the early stages of PD, there is a reduction in gait automaticity due to impairment of the sensorimotor circuit of the basal ganglia [35]. Therefore, patients with PD compensate by engaging in goal-directed networks to perform dual-tasks, instead of relying on the negatively affected habitual control pathway [36]. Discrepancies in performance between single- and dual-tasks could shed light on the underlying functional adaptation mechanisms, whether motor or cognitive. One study compared brain activity patterns in groups that focused on motor and cognitive functions, revealing increased activity in the prefrontal and parietal cortex of the cerebrum among the participants in the cognitive function-focused group [37]. This suggests that patients who prioritize cognitive function may leverage prefrontal cortex functions such as coordination, concentration, and execution in their efforts for behavioral enhancement. In such patients, enhancing the cognitive network may prove to be a more efficient strategy to improve gait and daily functional abilities than attempting to restore already lost motor functions. In PD, a higher cognitive reserve is associated with a lower overall cognitive impairment and reduced severity of motor symptoms [38, 39]. Motor reserves in PD explain the variations in motor deficits observed among patients despite having comparable levels of striatal dopamine depletion [40]. These concepts are expected to provide significant insights into the implementation of personalized rTMS interventions aimed at enhancing resilience against neurodegenerative changes.

Gait impairment in PD is one of the most disabling conditions and is associated with an increased risk of falls, reduced independence, and diminished quality of life [41, 42]. Improvements in simple motor symptoms, while beneficial, may not directly translate into functional enhancements that offer immediate benefits to patients with PD. The Timed-Up and Go (TUG) test in patients with PD is as an invaluable instrument to evaluate transitions, balance, and gait. In addition, when combined with gait analysis under both single- and dual-task conditions, the TUG test facilitates the quantitative assessment of overall gait function [42].

Hence, the variability in symptom improvement among patients with PD could be attributed to individual differences in motor and cognitive functional reserves. Consequently, designing effective rTMS treatment protocols necessitates a thorough assessment of each patient’s functional impairment and reserve capacity. Incorporating the concepts of motor and cognitive reserves into treatment planning allows for the tailoring of individualized rTMS protocols, optimizing treatment outcomes for patients with PD.

### Objectives {7}

The study aims to investigate the efficacy and safety of personalized rTMS in patients with PD, focusing on individual functional reserves to improve ambulatory function. The participants are categorized into motor or cognitive priority groups based on their functional reserve determined through single- and dual-task assessments, and specific rTMS strategies implemented that reflect their unique characteristics.

#### Trial design {8}

This is a prospective, exploratory, multi-center, single-blind, parallel-group, randomized controlled trial.

### Methods: participants, interventions, and outcomes

#### Study setting {9}

The study will be conducted across five tertiary hospitals in the Republic of Korea, including Samsung Medical Center, Seoul National University Hospital, and Yongin Severance Hospital as well as Bucheon St. Mary’s Hospital and St. Vincent’s Hospital, both of which are branches of the Catholic Medical Center. The study will be performed in accordance with the principles of Good Clinical Practice and the Declaration of Helsinki.

#### Eligibility criteria {10}

The inclusion criteria are as follows:Patients clinically diagnosed with idiopathic PD following the UK Parkinson’s Disease Society Brain Bank Diagnostic CriteriaModified Hoehn and Yahr scale 2 to 4Patients capable of walking on level ground without the use of a gait aidAged ≥ 50 yearsPatients who have provided informed consent and voluntarily signed the written consent form for participation in the study

The exclusion criteria include:Patients with contraindications for rTMS, a history of epilepsy, any metal inserted into the head, or who had undergone cranial surgeryPatients exhibiting cognitive impairment based on the Korean-Montreal Cognitive Assessment test, with the following cutoff scores [43]:< 7 points: Illiterate,< 13 points: Education duration 0.5–3 years,< 16 points: Education duration of 4–6 years,< 19 points: Education duration of 7–9 years, and< 20 points: Education duration 10 years or moreConcurrent major neurological conditions, such as spinal cord injury and strokeExisting significant psychiatric disorders requiring continuous medication, such as major depressive disorder, schizophrenia, bipolar disorder, or dementiaSevere dyskinesia or severe on–off phenomenonPregnancy and lactationParticipants with contraindications for MRI, such as those with implanted devices like pacemakersRefuse to participate in the study

#### Who will take informed consent? {26a}

The Korean Pharmacists Act mandates that a physician serving as the investigator should obtain informed consent from prospective clinical trial participants or their authorized representatives. Investigators are obliged to elucidate the contents of the finalized Institutional Review Board (IRB)-approved informed consent form to ensure a comprehensive understanding among potential research participants. This includes explaining the purpose of the study, the benefits, and harms involved and providing clear channels to contact both the investigator and the IRB for any questions that may arise during participation. Following consent acquisition, the investigator should promptly provide the participants with a copy of the consent form.

#### Additional consent provisions for collection and use of participant data and biological specimens {26b}

Not applicable. No biological specimens are collected.

## Interventions

### Explanation for the choice of comparators {6b}

The comparators of both sub-studies are the active control groups. The effectiveness of high-frequency rTMS applied to bilateral primary motor cortex in the upper limb (M1-UL) in patients with PD has been previously demonstrated to enhance general motor performance and alleviate depression and anxiety, aligning with evidence-based rTMS guidelines [9, 44]. Additionally, high-frequency stimulation of M1 has been shown to relieve musculoskeletal pain and improve the quality of life in patients with PD. Therefore, stimulation applied to bilateral M1 regions, as a conventional approach, is chosen as the comparative protocol to validate the superiority of this novel personalized rTMS.

### Intervention description {11a}

This study comprises two sub-studies, each designed as a two-arm trial. The participants are classified into sub-studies based on their functional reserves as follows:Motor priority group (sub-study 1): Patients with well-preserved motor function in whom motor skills have a significant impact on overall functioning; andCognitive priority group (sub-study 2): Patients with well-preserved cognitive function and notable impairment in motor function in which cognitive abilities substantially affect overall functioning.

As part of the pre-intervention assessment, the TUG and the TUG under cognitive dual-task condition (TUG-Cog) are administered. The TUG-Cog involves performing the TUG test concurrently with a cognitive task of serially subtracting the number 3. Additionally, serial 3 subtraction as a single cognitive task is performed from a randomly selected number between 80 and 100 for 20 s in the sitting position [34]. For both tasks, the correct response rate for subtraction is calculated as the time spent in seconds divided by the number of correct responses. Task-specific interference is calculated using the equation for dual-task effect (DTE) (Eq. 1) [37]. The motor dual-task effect (mDTE) is computed using stride length and the cognitive dual-task effect (cogDTE) is based on the correct response rate of TUG and TUG-Cog.1$$\text{Dual task effect} \left(\%\right)=\frac{(\text{Single task }-\text{ Dual task})}{\text{Single task}} \times 100$$

For evaluation of task prioritization during dual-task conditions, the modified Attention Allocation Index (mAAI) is employed (Eq. 2) [34]. The mAAI is calculated by subtracting the cogDTE from the mDTE, where negative values indicate an attention shift toward the motor task (motor priority), while positive values suggest an attention shift toward the cognitive task (cognitive priority).2$$\text{modified Attention Allocation Index }\left(\text{mAAI}\right)=\text{motor dual task effect}\left(\text{mDTE}\right)-\text{cognitive dual task effect }(\text{cogDTE})$$

Patients demonstrating motor priority will undergo high-frequency rTMS over the primary motor cortex in the lower limb (M1-LL), whereas those showing cognitive priority receive high-frequency rTMS over the left DLPFC. Given the substantial impairment of the motor network in the latter group, we envision a heightened reinforcement of compensatory mechanisms utilizing the cognitive network.

In the experimental group of sub-study 1, the more affected M1-LL is stimulated using a double-cone coil with a frequency of 10 Hz and an intensity set at 90% of the participant’s resting motor threshold (RMT) measured in the more affected M1-LL. The RMT in the M1-LL is determined at rest with the tibialis anterior muscle on the more affected side. The RMT is defined as the minimum intensity at which responses of 50 uV or greater are elicited in at least five out of ten trials, measured in a resting state of full relaxation. The more affected side will be determined based on the findings of the MDS-UPDRS Part III performed during at the pre-intervention evaluation. In instances where the assessment does not conclusively identify the more affected side, the onset side of PD symptoms is considered. If the side of onset remains unclear, the non-dominant side is designated as the more affected side. The stimulation protocol consisted of 5 s of stimulation followed by a 25-s rest period, repeated for a total of 20 cycles, resulting in the administration of 1000 stimuli per session. Using this protocol, each session lasts a total of 10 min.

In sub-study 2, the hot spot for the experimental group is the left DLPFC. The left DLPFC will be manually designated based on anatomical landmarks [45]. Once the left DLPFC is determined, the Neurophet tES LAB (Neurophet Inc., Seoul, Republic of Korea) will be used to obtain individual guide information relative to Cz. The software segments each individual’s T1-weighted brain image acquired at pre-intervention evaluation, reconstructs it into a three-dimensional brain model, and provides guidance for coil placement on the scalp. Investigators use the skull caps to apply stimulation at precise locations. The stimulation intensity is set at 100% of the participant’s RMT in the more affected M1-UL. Stimulation frequency, duration, cycles, and total stimuli are the same as those used in the experimental group in sub-study 1.

The bilateral M1-UL is stimulated in the control groups in both sub-studies. The stimulation intensity is adjusted to 90% of the participants’ RMT in the more affected M1-UL. The RMT of the M1-UL is determined at rest with the first dorsal interosseus muscle on the more affected side. Bilateral stimulation is conducted sequentially, starting with the more affected side, followed by the less affected side. A figure-eight coil will be used to stimulate the DLPFC and M1-UL. Other stimulation protocols are consistent with those used in the experimental groups. The stimulation intensity, frequency, duration, and total stimuli were determined based on previous study guidelines [44].

The intervention will employ a Magstim Rapid2 (Magstim Co. Ltd., UK) or MagPro X100 magnetic stimulator (MagVenture, Lucernemarken, Denmark). All participants will undergo 10 rTMS sessions, 2–3 times a week, for 10 min per session over a period of 4 weeks. After completing the initial five sessions within a 2-week period, a mid-intervention evaluation will be conducted. During each session, even-level gait training or treadmill training will be also performed for 10 min immediately after rTMS.

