### Outcomes {12}

Pre-intervention evaluations will be conducted within 3 days before the initial intervention session. Post-intervention evaluations will be conducted within 48 h after the final intervention session. Follow-up evaluations will be conducted 2 months after the intervention concludes. The primary outcome is the difference in TUG time between the pre- and post-intervention evaluations. Secondary outcome variables include the TUG measured at follow-up evaluations. Additionally, the TUG-Cog, MDS-UPDRS Part III, New Freezing of Gait Questionnaire (NFoGQ), Digit Span, trail-making test, transcranial magnetic stimulation-induced motor-evoked potential (TMS-induced MEP), diffusion tensor imaging (DTI), and rsfMRI are assessed pre-intervention, post-intervention, and at follow-up to investigate the effectiveness of personalized rTMS.

The TUG assesses ambulatory functions, including gait, balance, mobility, and fall risk. In the TUG, the participants are instructed to rise from a chair, walk to a traffic cone located 3 m away at a comfortable pace, return to the chair, and sit down. The TUG-Cog involves the simultaneous execution of the TUG test and serial subtraction in three, starting from a randomly selected number between 80 and 100 [34]. The TUG-Cog is designed to provide a comprehensive assessment by incorporating both motor and cognitive tasks. The TUG and TUG-Cog are each measured twice, and the mean values are utilized for analysis. During the TUG and TUG-Cog, the participants wore shoes equipped with a smart insole (Gilon Gait Data Collector & Analyze MD, Gilon Inc., Gyeonggi, Republic of Korea). The smart insole measures gait parameters including stride length, step count, cadence, velocity, distance, swing ratio, and foot plantar pressure (heel/mid/toe). The stride lengths of the TUG and TUG-Cog are utilized to assign sub-studies and evaluate the efficacy of the intervention. During the mid-intervention evaluation, the TUG is conducted without smart insoles.

The MDS-UPDRS part III assesses the motor symptoms of PD using 18 items, with each item scored on a scale of 0 to 4 [46]. Higher scores indicate more severe symptoms. The NFoGQ consists of nine items designed to assess the severity of freezing of gait (FoG) and gait disturbance [47]. The NFoGQ has demonstrated reliability in measuring both the severity of FoG and its functional impact in patients with PD.

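### The subtraction score behind sub-study assignment is seconds per correct answer: it is undefined at zero correct in TUG-Cog and, near zero, points to the wrong sub-study

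*Protocol article*

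**What the plan says.** All from the protocol article.

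- **Score.** Intervention description {11a} calls the measure a correct response rate and, for both subtraction tasks, states that "the correct response rate for subtraction is calculated as the time spent in seconds divided by the number of correct responses".
- **Seated task.** Serial-3 subtraction as a single task starts from a number "between 80 and 100 for 20 s in the sitting position".
- **Dual-task effects.** Eq. 1 is (single - dual) / single x 100. "The motor dual-task effect (mDTE) is computed using stride length", while "the cognitive dual-task effect (cogDTE) is based on the correct response rate of TUG and TUG-Cog".
- **Classification.** "The mAAI is calculated by subtracting the cogDTE from the mDTE, where negative values indicate an attention shift toward the motor task (motor priority"); positive values mean cognitive priority. Participant timeline {13} and Implementation {16c} place this classification at the pre-intervention evaluation, before treatment.
- **Walks.** In Outcomes {12} the TUG is to "walk to a traffic cone located 3 m away at a comfortable pace, return to the chair, and sit down", and TUG-Cog adds the subtraction to it. "The TUG and TUG-Cog are each measured twice, and the mean values are utilized for analysis".
- **Eligibility.** Eligibility criteria {10} excludes by education-specific K-MoCA cut-offs, the lowest being "< 7 points: Illiterate". No listed criterion concerns subtraction ability.

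No rule is given for zero correct answers.

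**The concern.** The sign of mAAI places each patient in one of two separate trials with different experimental stimulation sites. The rule therefore has to return a usable value for everyone who reaches it. Three features of the printed text stand in the way.

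1. The number of correct answers is the divisor, so a zero count during TUG-Cog yields no score, no cogDTE and no mAAI.
2. Seconds per answer rises as performance falls, whereas stride length falls. The same Eq. 1 therefore gives a cognitive cost a negative sign and a stride cost a positive one. A patient who nearly stops answering while walking gets a large positive mAAI and is labelled cognitive priority. By the index's own description, attention that moves to the walk is motor priority.
3. The sentence defining cogDTE names the plain TUG as a source, but nobody subtracts during the plain TUG.

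At stake is whether the sub-studies contain the patients they are meant to contain, and whether sites would treat an unscorable patient alike.

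**Working it through.** The protocol gives no figure on this point, so there is nothing to reproduce. Eq. 1 and Eq. 2 can be evaluated directly.

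**Step 1: the formula at and near zero.** Assumed patient: stride length 1.0 m single and 0.9 m dual; 8 correct in the seated 20 s; a 15 s TUG-Cog. Only the 20 s comes from the protocol.

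- mDTE = (1.0 - 0.9) / 1.0 x 100 = 10%.
- Seated score: 20/8 = 2.5 s per answer, or 8/20 = 0.4 answers per second.

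| Correct in TUG-Cog | cogDTE as printed | mAAI as printed | cogDTE, answers/s | mAAI, answers/s |
|---|---|---|---|---|
| 0 | undefined (limit: minus infinity) | undefined (limit: plus infinity) | 100% | -90 |
| 1 | -500% | +510 | 83.3% | -73.3 |
| 3 | -100% | +110 | 50% | -40 |
| 5 | -20% | +30 | 16.7% | -6.7 |
| 6 | 0% | +10 | 0% | +10 |
| 7 | 14.3% | -4.3 | -16.7% | +26.7 |

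For 3 correct as printed: 15/3 = 5 s, cogDTE = (2.5 - 5)/2.5 x 100 = -100%, mAAI = 10 + 100 = +110. With answers per second: 3/15 = 0.2, cogDTE = (0.4 - 0.2)/0.4 x 100 = 50%, mAAI = 10 - 50 = -40.

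With answers per second, a zero in TUG-Cog gives mAAI = mDTE - 100. This is negative whenever mDTE is below 100%, so the patient is classifiable as motor priority.

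**Step 2: the seated zero.** No correct answer in the seated task makes the single-task value undefined as printed and zero as answers per second. Eq. 1 divides by it, so cogDTE is undefined under either form.

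**Step 3: how often a TUG-Cog zero might occur.** The documents give neither subtraction speed nor TUG-Cog time, so everything here is assumption. For Poisson counts with mean L per walk:

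- At least one of two walks at zero (enough to break an average of per-walk scores): 1 - (1 - exp(-L))^2.
- Both walks at zero (needed to break a pooled score): exp(-2L).

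| L | At least one zero | Expected of 60 | Both zero | Expected of 60 |
|---|---|---|---|---|
| 2 | 25% | 15 | 1.8% | 1.1 |
| 3 | 10% | 6 | 0.25% | 0.15 |
| 4 | 4% | 2 | 0.03% | 0.02 |

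If answers are instead a fixed number of attempts, each 80% correct, the chance of at least one zero walk is 1 - (1 - 0.2^k)^2:

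- k = 3 attempts: 1.6% (Poisson with the same mean of 2.4: 17%).
- k = 4: 0.3% (Poisson, mean 3.2: 8%).
- k = 5: 0.06% (Poisson, mean 4: 3.6%).

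Very slow subtraction goes beyond this range. At 0.1 correct per second and an 8 s walk (L = 0.8), the Poisson figures are 70% for at least one zero and 20% for both.

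**Step 4: averaging against pooling.** Take 1 and 5 correct in two 12 s walks. As printed, the mean of ratios is (12/1 + 12/5)/2 = 7.2 s, but the pooled value is 24/6 = 4.0 s. With answers per second, (1/12 + 5/12)/2 = 0.25, the same as 6/24. For equal walk times, inverting the ratio removes the discrepancy.

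**The case against.** The strongest reply is that this is one inverted ratio, and that correcting it to match its name resolves most of the point: a TUG-Cog zero becomes scorable and the averaging discrepancy nearly vanishes. That is right, and it is why the remedy must start with the inversion. Scoring a zero as the motor-priority extreme while keeping seconds per answer would contradict the scale. The inversion leaves two items open, the seated zero and the mention of the plain TUG.

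A second reply is that edge-case handling may sit in the full protocol or an assessor manual, neither of which is shown. This stands against treating the missing zero rule as a fault in itself. It does not answer the printed formula, which is stated in the article and gives the wrong direction close to zero.

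A reader might infer that patients with no correct answer cannot be classified or randomised. The article states no such consequence. The walk is done twice, and K-MoCA cut-offs remove the most impaired patients, though they do not test subtraction.

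A reader might also infer that averaging per-walk ratios shifts patients without true interference into cognitive priority. Outcomes {12} does not say whether ratios are averaged or counts and times are pooled. The size of the shift also depends on the model. With mDTE centred on 0 (SD 10 points), Poisson counts with 3 to 5 expected answers gave about 56-57% cognitive priority, against 47-49% pooled. With 6 attempts per 10 s walk, 12 seated and 85% correct, it was about 53.5% against 51%.

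**Conclusion.** The point holds in a limited form. It is certain from the text alone that the score has no finite value at zero correct answers in TUG-Cog, that near zero it drives mAAI towards cognitive priority against the index's stated meaning, and that the plain TUG cannot supply a subtraction score. Because the sign of mAAI assigns the sub-study, the printed rule fails or misdirects such patients.

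How many are affected is not known. The range from well under 1% to about 25% assumes roughly two to four correct answers per walk. It moves with the count model and with averaging or pooling, and slower subtraction would exceed it. None of these figures should be read as an estimate for this trial. Exclusion of zero-count patients from randomisation and a systematic shift from averaging are not established. The correction is still worth making, because the formula decides allocation to sub-study and the change is small.

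**What to change.** In Intervention description {11a}:

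1. Define the score as correct responses divided by seconds. For TUG-Cog, use total correct answers over total time across the two walks. No correct answer then gives cogDTE = 100% and a classifiable patient.
2. Name the seated 20 s serial-3 task as the single-task leg of cogDTE and TUG-Cog as the dual-task leg. Remove the plain TUG from that sentence.
3. State in advance how a patient with no correct answer in the seated task is handled, since Eq. 1 is undefined there under either form.

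The cost is protocol wording and one eCRF formula, with no new measurement. The downside falls on participants already enrolled (Trial status gives an actual start of 20 February 2024). Their mAAI must be re-derived from recorded counts and times, and any whose sign changes should be reported.
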